#### Statistical analysis plan

Quantitative data analysis will be performed using SAS, STATA, and R software. Descriptive analyses of the community-based data will examine socio-demographic characteristics, health indicators, and healthcare behaviors of the program and comparison block samples at baseline and end-line. The quantitative evaluation of health and healthcare endpoints will focus on assessing changes in the continuum of care indicators and mean blood pressure in the community-based surveys. We will assess changes in baseline to end-line indicators of health outcomes (e.g., blood pressure) and changes in continuum of care indicators (e.g., proportion screened) for both the program and comparison blocks; see Table 2 for indicators. A simple difference-in-difference (DiD) [33] estimate for each indicator will be computed as
$$ \mathrm{DiD}=\left({p}_{g=\mathrm{i},\mathrm{t}=1}-{p}_{g=\mathrm{i},\mathrm{t}=0}\right)-\left({p}_{g=\mathrm{c},\mathrm{t}=1}-{p}_{g=\mathrm{c},\mathrm{t}=0}\right) $$where p indicates prevalence or mean of each indicator; *g* subscripts group (i = program; c = comparison); and t subscripts the time point of data (0 = pre-program; 1 = post-program). We will estimate log-binomial models (binary outcomes) or linear models (continuous outcomes, with log-transformation if needed) with robust variance to compute the DiD after accounting for compositional characteristics of the community and clustering of data within villages. For each outcome indicator separately, the following model will be estimated using individual-level data:
$$ \mathrm{Outcome}\ \mathrm{indicator}\sim \mathrm{program}\ \mathrm{group}+\mathrm{pre}-\mathrm{post}\ \mathrm{indicator}+\mathrm{program}\ \mathrm{group}\ \mathrm{x}\ \mathrm{pre}-\mathrm{post}\ \mathrm{indicator}+\mathrm{age}+\mathrm{sex}+\mathrm{education}+\mathrm{religion}+\mathrm{marital}\ \mathrm{status}+\mathrm{below}\ \mathrm{poverty}\ \mathrm{line}+\mathrm{facility}\ \mathrm{type}\ \left(\mathrm{public}\ \mathrm{versus}\ \mathrm{private}\right). $$

The coefficient associated with the interaction term, “program group x pre-post indicator,” is the adjusted DiD estimate accounting for heterogeneity in socio-demographic characteristics. The model will be estimated using generalized estimating equations (GEE) to account for clustering of outcomes within the villages (i.e. village is the cluster variable specified for statistical analysis). Sub-group analyses will examine differences by gender and socioeconomic status.

Data points recorded in the I-TREC system will be analyzed by month to examine trends over time and seasonality. We will also evaluate change patient outcomes over time (e.g., mean SBP change). While several of the I-TREC platform indicators are purely descriptive measures of performance (e.g., mean time for data upload), other indicators of healthcare delivery may be compared between I-TREC facilities and comparison group facilities (e.g., patient volume).

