## Background

Hypertension and diabetes together affect over 275 million Indians and their families [1]. These conditions are rising rapidly in all regions of India, commonly co-occur [2–4], and are associated with several adverse health outcomes—such as higher rates of death, myocardial infarction, stroke, blindness, kidney failure. Yet, both hypertension and diabetes are treatable such that timely and appropriate therapy mitigates associated morbidity due to complications and premature mortality. While lack of diagnosis is among the major obstacles to seeking appropriate treatment [5, 6], treatment outcomes even after diagnosis are far from ideal. Less than half of individuals who have hypertension and diabetes in the community are aware of their condition [7, 8], and only 20–25% achieve adequate blood pressure [9] or blood glucose control [10]. Under-diagnosis, under-treatment, and poor control for both hypertension and diabetes are disproportionately high in rural settings [11, 12], where the majority of the Indian population resides.

India’s rural healthcare system is currently organized as a hierarchy of facilities that range from relatively lower-skilled personnel supported by simple infrastructure at the village level to relatively higher-skilled personnel supported by sophisticated infrastructure at the district level. This model attempts to maximize geographical coverage by allowing for “up referrals” and “down referrals” across levels of the healthcare system so that the demand of the individual patient can be met by appropriate resources, such as skilled human resources, infrastructure and services. The referral linkages between these institutions, while theoretically in place, are not implemented efficiently or cohesively. In practice, patients access any level of the healthcare system convenient for them, resulting in a mismatch between patient needs and resource availability. Challenges to the system are compounded by the heterogeneity of treatment guidelines, diagnostic modalities, and medications [13–17] needed at all levels of health care to appropriately serve the growing population with NCDs alongside the large population seeking care for maternal and child health and infectious diseases [18–21].

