#### Outcomes

Program indicators are guided by the Reach, Effectiveness, Adoption Implementation, and Maintenance (RE-AIM) framework [31]. The principal endpoints for evaluation are shown in Table 2, and focus on the domains of reach, effectiveness, adoption, and implementation of the program components. Reach and effectiveness will be assessed using a combination of community-based data and facility-based data. For example, the proportion of adults ages 30 and older in the community who are screened for hypertension is a measure of reach that will be obtained through a representative community survey. A second measure of reach is the number of patients seeking care for hypertension and diabetes who have an eCRF, which will be measured through health facility data. Similarly, effectiveness will be assessed through health outcomes (e.g., reductions in mean blood pressure and/or mean blood glucose) among patients attending program facilities and also among adults with hypertension and/or diabetes in the community. Adoption metrics focus on healthcare provider utilization of the eCRF and CDSS tools. Implementation measures focus on quantifying the proportion of patients who receive care through the eCRF and CDSS tools. Finally, maintenance will be assessed through qualitative research with stakeholders within the health system to understand views of sustainability.

**Table 2 Tab2:** Key outcome indicators for the I-TREC evaluation

RE-AIM domain	Key indicators
**Reach**	Proportion of adults ages 30 and older in the community screened for hypertension by a government healthcare provider
	Proportion of adults ages 30 and older in the community screened for diabetes by a government healthcare provider
	Number of patients seeking care for hypertension and diabetes at a government health facility who have an eCRF
**Effectiveness**	Reduction in mean blood pressure in patients receiving care in program facilities
	Reduction in mean blood glucose in patients receiving care in program facilities
	Proportion who achieve blood pressure and blood glucose control among patients receiving care in program facilities
	Proportion who achieve blood glucose control among patients receiving care in program facilities
	Reduction in mean blood pressure in the community
	Reduction in mean blood glucose in the community
	Proportion of hypertension patients who achieve blood pressure control in the community

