#### Pre- and post-program quantitative cross-sectional community surveys

The community-based evaluation component will assess whether the I-TREC program has an impact on blood pressure and blood glucose awareness, treatment seeking, and control among adults in the community. This evaluation component is critical to learning the real-world impact of the I-TREC program on community-level indicators of the care continuum (screening, treatment, control). Data collected in the program and comparison blocks prior to the program will be compared with data collected from these same blocks after the program using identical procedures. This design allows us to assess and address several threats to validity, including lack of temporal order, comparability across the two blocks (leading to potential confounding by population composition) and secular changes unrelated to our program that affect study endpoints (leading to potential confounding by external factors). Given that we will be sampling separate cross-sections of the population in each group and time point, we do not expect inference to be affected by population aging (maturation threats) over the 3-year program period.

At baseline—prior to intervention—we employed a multi-stage cluster sampling design to obtain a representative sample of adults aged 30 years and older in both blocks under study. Within each block, census data were used to select villages proportionate to population size and subsequently we conducted household mapping and listing to generate a sampling frame for households. Households were selected using systematic random sampling, and one adult man and woman from each household were randomly selected using the Kish method to achieve the desired sample size. At endline, this same procedure will be repeated.

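### For binary community indicators, the log-binomial interaction coefficient that the plan calls the adjusted DiD is a log ratio of prevalence ratios, not the additive DiD that the plan defines

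*Protocol article*

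**What the plan says.** The Statistical analysis plan section of the protocol article makes three statements that bear on this point.

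- The estimand: "A simple difference-in-difference (DiD) [33] estimate for each indicator will be computed as" the program block's change minus the comparison block's change, "where p indicates prevalence or mean of each indicator". For a binary indicator this is a number of percentage points.
- The model: "We will estimate log-binomial models (binary outcomes) or linear models (continuous outcomes, with log-transformation if needed) with robust variance to compute the DiD", with adjustment for population composition and for clustering by village.
- The reported quantity: the coefficient of program group by pre-post indicator "is the adjusted DiD estimate accounting for heterogeneity in socio-demographic characteristics". No distinction is drawn between binary and continuous outcomes. No predicted prevalences, identity link or back-transformation is mentioned.

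Table 2 (Outcomes) lists four binary indicators measured in the community: screening for hypertension, screening for diabetes, blood pressure control and blood glucose control. The first reads "Proportion of adults ages 30 and older in the community screened for hypertension by a government healthcare provider".

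**The concern.** The article defines one quantity and then gives its name to another. This is a conflict within the current text, not a detail left to a fuller plan, because the article says outright which coefficient is the DiD.

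Three things follow for the binary indicators.

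- The adjusted result has a different unit and a different null hypothesis from the simple DiD for the same indicator.
- A reader who sees the two differ would put the gap down to covariate adjustment, when part or all of it may be the change of scale.
- Where baselines differ, parallel trends on one scale generally means non-parallel trends on the other, so the two analyses rest on different identifying assumptions.

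The blocks were not randomised. The community survey section itself lists as a threat to validity "comparability across the two blocks (leading to potential confounding by population composition". The community survey is also the main source for comparing outcomes between blocks, because the Summary says the comparison block has no patient data comparable with the eCRF.

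**Working it through.** The article gives no figure for a binary DiD, so there is none to reproduce. The check is algebra, followed by illustration with assumed rates. Baseline rates by block are not given. The only anchor for control is the Background's general statement that "only 20–25% achieve adequate blood pressure", which describes India and not these two blocks.

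**Algebra.** Write i for program, c for comparison, 0 for before and 1 for after.

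- Defined DiD = (p_i1 − p_i0) − (p_c1 − p_c0).
- Log-link interaction, without covariates = ln(p_i1/p_i0) − ln(p_c1/p_c0) = ln[(p_i1/p_i0)/(p_c1/p_c0)].

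Adding covariates makes the second quantity conditional on them. It does not return it to the additive scale.

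**Assumed rates**

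| Program | Comparison | DiD | Ratio of ratios | Log coefficient |
|---|---|---|---|---|
| 30% → 45% | 10% → 20% | 15 − 10 = +5 points | 1.50/2.00 = 0.75 | −0.288 |
| 20% → 28% | 10% → 16% | 8 − 6 = +2 points | 1.40/1.60 = 0.875 | −0.134 |
| 25% → 35% | 20% → 28.5% | 10 − 8.5 = +1.5 points | 1.40/1.425 = 0.982 | −0.018 |
| 20% → 28% | 25% → 34% | 8 − 9 = −1 point | 1.40/1.36 = 1.029 | +0.029 |
| 20% → 28% | 20% → 26% | 8 − 6 = +2 points | 1.40/1.30 = 1.077 | +0.074 |

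The last row has equal baselines, and there the signs agree.

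**Fitted models.** Data were built with the second row's rates, 1,750 adults per cell and 35 villages per block. The identity-link GEE interaction was +0.0200 and the log-link one −0.1335, on the same data.

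**How often the signs differ.** In an assumed grid, the comparison baseline is 20%, the program baseline is higher by a fixed gap, and each block's rise is uniform between 0 and 15 points. The signs disagreed in 0% of scenarios at no gap, 4.6% at 2 points, 9.9% at 5 points and 16.7% at 10 points.

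**Size against sampling error.** Take 3508/2 = 1754 per block, assumed to apply to each wave. After 10% refusal this leaves 1754 × 0.9 = 1579. With 20% having diagnosed hypertension, about 316 per cell contribute to blood pressure control. Ignoring clustering, the 95% intervals are:

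- 25% → 35% against 20% → 28.5%: DiD +1.5 points (−8.2 to +11.2); ratio 0.98 (0.68 to 1.42).
- 20% → 28% against 25% → 34%: DiD −1.0 point (−10.7 to +8.7); ratio 1.03 (0.71 to 1.50).

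For a screening indicator all 1579 adults per cell count. For 30% → 45% against 10% → 20%, ignoring clustering, the DiD is +5 points (+0.9 to +9.2) and the ratio 0.75 (0.61 to 0.92). Both intervals exclude their null, in opposite directions.

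**The case against.** A reader might infer that the trial's main result is at risk. The documents do not support that. The survey was sized on systolic pressure, and with an untransformed linear model the interaction coefficient is exactly the adjusted additive DiD. Continuous outcomes come in only if the optional log-transformation is used.

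A reader might also infer that conclusions would commonly reverse, or that a ratio below 1 shows harm. Neither follows.

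- Near 20–25%, with the cell sizes above, both scales show no detectable effect and the signs differ only within noise of about ±10 points.
- The sizeable reversal needs an assumed threefold baseline gap. The article gives no baselines by block and says neighbouring blocks in one district were chosen for comparability.
- In that example program screening still rises 1.5-fold. A ratio of 0.75 means a smaller relative gain than in the comparison block.

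Two further points count against a strong reading. The simple additive DiD is planned for each indicator, so a clash of sign would be visible. And whether trends are more nearly parallel in absolute or relative terms is a substantive question that the documents do not settle, so a relative estimand would be legitimate if declared.

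All of this limits the scope and likely size. It does not remove the conflict. The simple DiD is unadjusted and cannot stand in for the adjusted one, and the text neither declares a relative estimand nor describes a conversion. The phrase about computing the DiD from the models could be stretched to cover post-estimation prevalences, but the later statement that the coefficient itself is the adjusted DiD closes off that reading.

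**Conclusion.** The point holds as a mismatch between the defined estimand and the reported quantity, for the four binary community indicators and for other binary care-continuum measures put through the same model. Followed exactly, the plan would report under the name DiD a number in the wrong unit and with a different null. That part is algebra and needs no assumption.

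A change of sign is possible, not inevitable. It needs unequal baselines and change in the same direction in both blocks, and how likely it is depends on rates that the article does not give. All the illustrative rates here are assumptions. Mean SBP on its original scale is unaffected. The facility-based control indicators fall outside this model, since they have no comparison-block data. The correction is worth making before the endline analysis, so that the scale is not chosen after the results are seen.

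**What to change.** State that the adjusted DiD for binary indicators is on the additive scale already defined, and obtain it in one of two ways:

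- keep the log-binomial model, standardise the four group-by-time prevalences over the covariates, difference them, and give a village-level confidence interval by the delta method or a cluster bootstrap; or
- fit the GEE with an identity link and village-robust variance, so that the interaction is itself the adjusted DiD.

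Label any log-link interaction, once exponentiated, as a ratio of prevalence ratios. It may be reported alongside. If a continuous outcome is log-transformed, either convert the result to the original scale or label it as a ratio of geometric-mean ratios.

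The cost is a sentence or two in the analysis plan and a few lines of code. Sample size and data collection do not change.

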#### Patient flow under I-TREC

Figure 2 depicts patient flow within and across facilities in the I-TREC program. Following NHM and NPCDCS recommendations, all adults aged ≥30 years are eligible for universal screening of hypertension and diabetes in the community and opportunistic screening in health facilities by government health providers. At the village-level Sub-Centre, the lowest level of the healthcare facility hierarchy, the ANM is tasked with screening adults to identify suspected cases of hypertension and diabetes in the community. ANMs enter screening results into the “ANM portal” using a tablet-based application. Adults who are suspected to have hypertension and/or diabetes are referred to the nearest Primary Health Centre, the second level of the healthcare hierarchy, for diagnosis and treatment (see Table 1 and Fig. 2).

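### The adjusted DiD model conditions on public versus private facility, which the program can change, so its interaction term need not estimate the total community effect

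*Protocol article*

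**What the plan says.** In the protocol article, section Statistical analysis plan, two estimates are planned for the two-block comparison.

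- A simple DiD without covariates: a DiD "estimate for each indicator will be computed as" the change in the program block minus the change in the comparison block.
- An adjusted DiD from a regression: "For each outcome indicator separately, the following model will be estimated using individual-level data". The model contains block, wave, their interaction, age, sex, education, religion, marital status, below-poverty-line status and, last, facility type (public versus private).

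The same section gives the purpose of the regression: "to compute the DiD after accounting for compositional characteristics of the community and clustering of data within villages". It then says that the interaction coefficient "is the adjusted DiD estimate accounting for heterogeneity in socio-demographic characteristics".

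Three other places bear on the last covariate.

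- Pre- and post-program quantitative cross-sectional community surveys: the survey is to show whether the program "has an impact on blood pressure and blood glucose awareness, treatment seeking, and control among adults in the community". Each wave is a fresh sample of adults aged 30 and older.
- Patient flow under I-TREC: "Adults who are suspected to have hypertension and/or diabetes are referred to the nearest Primary Health Centre".
- Outcomes, Table 2: a reach indicator is "Proportion of adults ages 30 and older in the community screened for hypertension by a government healthcare provider", with a matching one for diabetes.

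**The concern.** Six of the seven covariates describe who lives in the block. Facility type describes where people go for care. The stated purpose of the adjustment covers the first six and not the seventh.

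The difference matters because I-TREC is delivered in government facilities and its screening step sends suspected cases to them. Endline facility type can therefore be a result of the program, and it overlaps with treatment seeking, which the survey is meant to assess as an outcome. Holding it fixed removes whatever part of the effect works by moving people into public care. It also compares public users at endline with public users at baseline, although the program may have changed who they are, and this can add selection bias.

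The two government-screening indicators are the most exposed, because bringing people into contact with government providers is what they measure. What is at stake is the meaning of the adjusted estimate: the effect on the community, or only the part of it that remains once facility choice is held constant.

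**Working it through.** The article states no figure on this point, so there is none to reproduce. The size can only be illustrated.

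**Formula.** Take a linear model and leave the socio-demographic covariates aside. Let D_Y be the DiD in the outcome without facility type, D_s the DiD in the public share s, and b the fitted facility-type coefficient. Block, wave and their interaction saturate the four cells, so least squares gives

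DiD with facility type = D_Y − b × D_s,

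where b is the within-cell public-minus-other difference, averaged over the four cells with weights s(1 − s) when the cells are of equal size. If D_s = 0, the two models agree.

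**Inputs.** All are assumed. The 30% starting public share borrows a number from the section Health outcomes among patients receiving the I-TREC program. There it is the share of the program block's population expected to seek government care, not a measured pre-program share. The comparison block stays at 30% throughout.

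**Case A: government screening, extreme.** Screening is 70% in public users and 10% in others in every cell. Public use in the program block rises from 30% to 50%.

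- Baseline in both blocks, and comparison at endline: 0.30 × 0.70 + 0.70 × 0.10 = 0.28
- Program at endline: 0.50 × 0.70 + 0.50 × 0.10 = 0.40
- D_Y = (0.40 − 0.28) − (0.28 − 0.28) = +0.12
- b = 0.60 and D_s = 0.20, so with facility type: 0.12 − 0.60 × 0.20 = 0

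On the ratio scale of the planned log-binomial model, the same inputs give 0.40/0.28 = 1.43 without the term and 1.00 with it.

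**Case B: government screening, milder.** Screening is 60% in public users (70% in the program block at endline) and 5% in others. For a 10-point rise in public use:

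- Baseline: 0.30 × 0.60 + 0.70 × 0.05 = 0.215
- Program at endline: 0.40 × 0.70 + 0.60 × 0.05 = 0.310
- D_Y = 0.095
- b = (3 × 0.21 × 0.55 + 0.24 × 0.65) / (3 × 0.21 + 0.24) = 0.5025 / 0.87 = 0.578
- With facility type: 0.095 − 0.578 × 0.10 = 0.037

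| Rise in public use (points) | DiD without facility type (points) | DiD with facility type (points) |
|---|---|---|
| 0 | 3.0 | 3.0 |
| 5 | 6.3 | 3.4 |
| 10 | 9.5 | 3.7 |
| 20 | 16.0 | 4.4 |

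**Case C: systolic blood pressure.** The program lowers SBP by 4 mmHg at a given facility type, and public users differ from others by b. Without facility type the DiD is −4 + b × D_s; with it, −4.

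| Rise in public use (points) | Without the term, b = −5 | Without the term, b = +3 | With the term, either b |
|---|---|---|---|
| 0 | −4.00 | −4.00 | −4.00 |
| 5 | −4.25 | −3.85 | −4.00 |
| 10 | −4.50 | −3.70 | −4.00 |
| 20 | −5.00 | −3.40 | −4.00 |

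If public users have lower pressure, the adjusted model understates the total effect. If they have higher pressure, it overstates it.

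**The case against.** The strongest reply is that the total effect is not lost. The simple DiD contains no facility type, so a gap between it and the adjusted DiD would be visible, and the article does not name the adjusted estimate as primary. This stands. But the simple DiD lacks the socio-demographic adjustment that the article wants for separate cross-sections, and no specified model gives a total effect with that adjustment.

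A second reply is that the term guards against shifts in facility use that the program did not cause, such as the closures of lower-tier facilities described under Current status. Stable block differences and shifts common to both blocks already cancel in a DiD. For a differential shift, conditioning on observed facility use cannot tell the program's part from the rest.

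Several stronger readings are tempting, and the documents do not support them.

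- A reader might infer that adults who sought no care are certain to drop out. The article does not define facility type; the full protocol could give it a level for non-users. The loss follows only if such adults have no value.
- A reader might infer that the bias always runs towards no effect. Case C shows otherwise for blood pressure.
- A reader might infer that the covariate is practically the same thing as the government-screening outcome. Auxiliary nurse midwives screen in the community, so a user of private care can be screened by a government provider. The two are related, not identical.
- A reader might infer that all of Table 2 is affected. Program-only measures, such as portal log-ins or upload time, have no comparison-block counterpart and cannot enter this model.

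**Conclusion.** The point holds for the adjusted DiD of the community-survey indicators. The model as written includes a variable that does not match the stated purpose of the adjustment and that the program can change. Where it does so, the interaction coefficient is not the total community effect.

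The clearest consequence is attenuation of the two government-screening indicators: +12 points to 0 if the whole gain comes from a 20-point rise in public use, and 9.5 to 3.7 points for a 10-point rise with some gain inside public care as well. For mean SBP the illustrated difference is at most 1 mmHg, in either direction; for glucose and the control indicators the direction is likewise not fixed.

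These sizes rest on assumed inputs and a linear working model. They need a differential shift in facility use together with an association between facility type and the outcome. The article does not say how large a shift to expect, and the listed components also act on care inside public facilities. It would therefore go too far to say that the plan adjusts the program effect away: it can remove part of it, and with no shift it removes none.

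**What to change.** Remove facility type from the main adjusted DiD model for the community-survey indicators. Keep age, sex, education, religion, marital status and below-poverty-line status, so that the model matches its stated purpose.

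Analyse use of public facilities as a DiD outcome in its own right; this shows directly whether the program moved people between sectors. If results by facility type are wanted, report them as descriptive or as a sensitivity analysis, define the variable, and include a category for adults who sought no care so that the all-adult denominators are kept.

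The change deletes one model term and needs no new data or sample. The cost is a small loss of explained variance. It is best made before the endline data are analysed.
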